## 4. Participants

### 4.1. Inclusion criteria

Patients 18-years-old or olderIsolated myocardial revascularization procedureSymptomatic patients with double- or triple-vessel coronary artery disease, including proximal or mid-LAD involvement, and angiographic diameter stenosis >70% by visual analysis in all territories (or ≥50% for the left main), with suitable target vessels presenting coronary diameter ≥1.5 mm, requiring surgical myocardial revascularization; symptomatic patients with angiographic stenosis <70% by visual estimation but with invasive or non-invasive evidence of flow-limiting ischemia in all three coronary territories are also eligible for inclusion.Total SYNTAX score > 22 or low Syntax score unsuitable for PCIClinical and anatomic eligibility for both minimally invasive and conventional CABG surgery as agreed to by surgical team.Silent ischemia, stable angina, unstable angina or recent MIIf recent MI, cardiac biomarkers must have returned to normal prior to randomization or cardiac troponin levels decreasing from a previous documented peak, consistent with the subacute phase of myocardial infarction and absence of ongoing ischemic injury.Ability to sign informed consent and comply with all study procedures

### 4.2. Exclusion criteria

ReoperationNeed for any concomitant cardiac surgery other than CABG (e.g., valve surgery, aortic repair, etc.), or intent that if the patient randomizes to surgery, any cardiac surgical procedure other than isolated CABG will be performedLeft ventricle disfunction (EF < 40%)Severe Chronic Pulmonary obstructive disease defined as Severe (GOLD 3): FEV₁ 30–49% predictedRenal failure disease defined as estimated glomerular filtration rate (eGFR) <60 mL/min/1.73 m².Emergency surgeryObesity class II or higher (body mass index >35 kg/m²)Sternum anatomic defects including pectus excavatumPeripheral vascular disease defined as significant femoral/iliac obstructive disease precluding safe peripheral cannulation for CPB (clinical/imaging judgment)Ascending aorta severe calcificationNon cardiac co-morbidities with life expectancy less than 1 year

As there is not yet an established institutional workflow specifically for MICS patients, our standard preoperative protocol does not routinely include chest CT imaging. Therefore, CT scans of the aorta and major vessels may occasionally be performed after randomization but before surgery. This occurs mainly in elective patients, due to scheduling constraints and the convenience of completing imaging during hospitalization, and in urgent cases such as patients admitted with acute coronary syndromes. If significant aortic calcification or femoral artery stenosis is identified, the patient is excluded prior to surgery and recorded as a scree failure.

This approach ensures patient safety while preserving the integrity of randomization, as no surgical intervention occurs before exclusion.

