## 3. Methods and analysis

### 3.1. Study design

This is a single-center, prospective, randomized controlled pilot trial, conducted over 30 months. A total of 100 patients will be randomized to undergo either to minimally invasive CABG through left anterior thoracotomy in the 4^th^ or 5^th^ intercostal space or conventional median sternotomy CABG. The use of CPB will be at the discreet of the surgeon.

Patients will be randomized in a 1:1 ratio using variable block sizes (blocks of 4–8), generated and managed electronically within the REDCap platform. This method ensures balance between groups while minimizing the predictability of the next allocation. The randomization module was configured by an independent researcher not involved in patient enrollment or surgery. Participants will only be randomized after meeting all eligibility criteria and signing the informed consent form.

All patients will be operated on by the same surgical team, with the standardized technique, at a high-volume tertiary cardiac surgery center.

Informed consent approved by our institutional research and ethics in committee under the number CAAE: 54175921.8.0000.0068, will be applied to all participants prior to surgery.

Post-operative follow up will be of 6 months. The postoperative evaluations will be divided into an outpatient presential evaluation around 1 month from discharge, followed by telephone contact 6 months. Follow up maybe extended up to 2 years after the surgery by telephone contact, to collect descriptive mid-term data, depending on institutional feasibility and patient availability.

This protocol follows the SPIRIT 2013 guidelines for randomized clinical trial protocols. The SPIRIT schedule of enrolment, interventions, and assessments is shown in Fig 1.

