### 4.3. Eligibility assessment

Clinical and anatomic eligibility for both minimally invasive and conventional CABG is determined by the coronary surgical team. The assessment includes coronary angiographic evaluation (SYNTAX score and target vessel distribution), ventricular function, comorbidities, and overall clinical stability.

Anatomic suitability requires the presence of good distal coronary targets (diameter >1.5 mm) and, whenever predictable from coronary angiography, the avoidance of intramyocardial coronary targets, as well as the potential for achieving complete revascularization based on coronary anatomy.

Other prerequisites include the absence of significant calcification or stenosis in the ascending aorta, its major branches, and femoral arteries (to evaluate the feasibility of peripheral cannulation for cardiopulmonary bypass if required). Preoperative chest CT is reviewed to assess thoracic anatomy, lung expansion, and parenchymal conditions. Patients with sternal deformities precluding either surgical approach are excluded.

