## 8. Sample size and statistical analysis

This is a pilot, exploratory randomized study comparing two surgical strategies (MICS vs. conventional CABG). The primary objective is to obtain descriptive estimates of event rates (rather than on hypothesis testing), between-group differences, and variability of outcomes to guide the design of a subsequent phase III trial.

The sample size of 100 patients (50 per group) was determined by operational feasibility and expected precision, rather than hypothesis testing. Assuming a conservative 8% 30-day MACCE rate (consistent with the average reported for conventional CABG in the 2025 ESC/EACTS Guidelines) the 95% confidence interval (Wilson) has a half-width of approximately ±5% in the overall cohort and ±7–8% per arm.

This approach aligns with published pilot trials in hybrid or minimally invasive CABG, which typically include 80–120 participants and use similar precision-based rationales.

Categorical variables will be presented as frequencies and percentages, and compared using the Chi-square or Fisher’s exact test, as appropriate. Continuous variables will be expressed as mean ± standard deviation or median (interquartile range) and compared using the Student’s t-test or Wilcoxon rank-sum test. Time-to-event outcomes (e.g., MACCE-free survival) will be analyzed using the Kaplan-Meier method.

No imputation for missing data will be performed, as this is a pilot trial focused on descriptive analyses rather than formal hypothesis testing. Missing data will be reported transparently, and analyses will be conducted using available cases.

All analyses will be performed according to the intention-to-treat principle. Participants randomized to the minimally invasive CABG group who require conversion to full sternotomy will remain in the MICS CABG arm for all primary and secondary outcome analyses. Conversion events will be reported descriptively, including their timing and reasons.

The decision to use or avoid cardiopulmonary bypass (on-pump or off-pump) will be left to the operating surgeon, according to intraoperative findings.

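### Randomized patients removed on a post-allocation CT are recorded as screen failures, which contradicts Sections 3.1 and 8 and can inflate the primary feasibility rate

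*Protocol article*

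**What the plan says.** Section 3.1 (Study design) sets the order of events: "Participants will only be randomized after meeting all eligibility criteria and signing the informed consent form".

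Section 4.2 (Exclusion criteria) departs from that order. It explains that "As there is not yet an established institutional workflow specifically for MICS patients, our standard preoperative protocol does not routinely include chest CT imaging", and that as a result "CT scans of the aorta and major vessels may occasionally be performed after randomization but before surgery". The consequence follows: "If significant aortic calcification or femoral artery stenosis is identified, the patient is excluded prior to surgery and recorded as a scree failure". The section defends this: "This approach ensures patient safety while preserving the integrity of randomization, as no surgical intervention occurs before exclusion".

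Section 4.3 (Eligibility assessment) describes the same imaging as part of deciding eligibility: "Preoperative chest CT is reviewed to assess thoracic anatomy, lung expansion, and parenchymal conditions". It also lists freedom from significant disease of the ascending aorta and femoral arteries among the prerequisites.

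Section 8 states: "All analyses will be performed according to the intention-to-treat principle". It says that MICS patients "who require conversion to full sternotomy will remain in the MICS CABG arm for all primary and secondary outcome analyses", but does not mention patients removed on CT. Section 6.1 defines primary feasibility as completing the planned minimally invasive strategy without conversion to sternotomy.

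**The concern.** A screen failure is a patient who never reached randomization. Under Section 4.2 the label goes to patients who have already been allocated, and it takes them out of the set that Section 8 promises to analyse.

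The stated justification rests on the wrong event. The comparison is protected by the act of allocation, not by the first incision. Removal after allocation is harmless only if it cannot depend on the arm, and the protocol describes no safeguard for that:

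- No rule requires the same imaging in both arms.
- No rule requires the CT to be read blind to allocation. Eligibility is judged by the coronary surgical team (Section 4.3).
- The femoral criterion in Section 4.2 is partly a matter of judgment. The aortic criterion is worded as severe calcification in the exclusion list but as significant calcification in the post-randomization rule.
- On-pump MICS uses femoral cannulation (Section 5.1) and on-pump sternotomy uses central cannulation (Section 5.2). A femoral finding therefore bears mainly on the MICS arm.

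At stake first is the feasibility rate. A patient allocated to MICS whose anatomy then rules it out did not complete the planned strategy, yet leaves the denominator. The plan retains one kind of non-completion (conversion) and deletes another. The 30-day safety comparison is also exposed if removal differs by arm. Since the pilot is meant to guide a phase III design, loss between allocation and surgery is itself something it should measure.

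**Working it through.** **1. The statements side by side.** Section 3.1: all criteria are met, then the patient is randomized. Section 4.2: the patient is randomized, then the imaging bearing on two exclusion criteria may be obtained, then the patient may be removed. Section 8: all analyses are intention-to-treat. A patient removed under Section 4.2 was randomized without having been shown to meet all criteria (against 3.1) and is not analysed as randomized (against 8). Sections 4.2 and 4.3 also differ on whether preoperative chest CT is a regular part of the work-up.

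**2. The plan's own figure.** Section 8 gives a 95% Wilson half-width at an 8% event rate of about ±5% overall and ±7–8% per arm. With z = 1.96,

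half-width = z·√[p(1−p)/n + z²/(4n²)] / (1 + z²/n).

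- n = 100: 5.4 points (interval 4.1% to 15.0%).
- n = 50: 7.8 points (interval 3.2% to 18.8%).

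Both agree with Section 8. With 45 patients in an arm the half-width is 8.3 points, so lost precision is minor. The issue is which patients are counted.

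**3. Effect on the feasibility rate.** Inputs:

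- N = 50 randomized to MICS (Section 8, 50 per group).
- 2 conversions, assumed. This is 4%, close to the 3.8% of a published series cited in Section 1.2; it is not a design assumption of the trial.
- k = MICS patients removed on post-randomization CT. The protocol does not give k, so a range is shown.

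Successes s = N − k − 2. Reported rate = s/(N − k). All-randomized rate = s/N. The difference is

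s/(N − k) − s/N = [s/(N − k)] × (k/N),

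that is, the reported rate times the fraction dropped. For k = 1: 0.959 × 1/50 = 1.9 points.

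| k | Removed patients dropped | All randomized to MICS | Difference (points) |
|---|---|---|---|
| 0 | 48/50 = 96.0% | 48/50 = 96.0% | 0 |
| 1 | 47/49 = 95.9% | 47/50 = 94.0% | 1.9 |
| 2 | 46/48 = 95.8% | 46/50 = 92.0% | 3.8 |
| 3 | 45/47 = 95.7% | 45/50 = 90.0% | 5.7 |
| 5 | 43/45 = 95.6% | 43/50 = 86.0% | 9.6 |

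The protocol does not say whether removed patients are replaced. If they are, so that 50 are operated and 48 succeed, the reported rate stays at 96.0%. The all-randomized rate is then 48/51 = 94.1%, 48/52 = 92.3%, 48/53 = 90.6% and 48/55 = 87.3% for k = 1, 2, 3 and 5. The differences are 1.9, 3.7, 5.4 and 8.7 points.

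**4. Scale.** The 2 assumed conversions cost 4 points. Two CT removals shift the rate by nearly as much (3.7 to 3.8), and three by more (5.4 to 5.7).

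**The case against.** Four counter-arguments deserve weight.

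*Removal may not depend on the arm.* Section 4.2 names no arm, and its reasons for late CT are scheduling, convenience during admission and urgent presentation. Aortic calcification also matters in the sternotomy arm, where on-pump cases use aortic cannulation and cross-clamping (Section 5.2). A reader might infer that the MICS arm sheds its higher-risk vascular patients while similar patients stay in the sternotomy arm, so that MACCE is biased in favour of MICS. The documents do not support that as a statement of fact. Differential removal is possible because no safeguard excludes it, but it is not documented. Any effect may also be small. If 5 of 55 MICS patients were dropped and their risk were 16% rather than 8% (both assumed), the arm's rate would be (50 × 0.08 + 5 × 0.16)/55 = 8.7% instead of 8.0%. That is 0.7 points against a half-width of 7 to 8. This stands, so the MACCE point is conditional.

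*The findings are baseline criteria.* Removing patients who were never eligible can be defended when both arms are imaged alike and judged blind to allocation, and a CT-eligible denominator is a legitimate target. The protocol provides neither safeguard and declares intention-to-treat, so that denominator belongs in a sensitivity analysis.

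*The count is unknown and may be small.* This is true. The protocol describes late CT as occasional, and Section 3.2 counts only patients who completed surgery. The size therefore stays a range that starts at zero.

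*Imaging everyone before randomization is not free.* A reader might infer from Section 4.3 that every patient already has the CT and that only its order need change. Section 4.2 says chest CT is not routine, so a universal requirement could add imaging. This stands and limits the fix.

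**Conclusion.** The point holds as a contradiction in the current text, whatever the number of patients involved. Section 4.2 cannot be reconciled with Sections 3.1 and 8, and its claim that the integrity of randomization is preserved does not follow from the absence of surgery.

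For feasibility, dropping MICS-allocated patients can raise the reported rate by about 1.9 points per patient relative to all patients randomized to MICS. This assumes about 50 MICS patients, 2 conversions, and removed patients counted as not completing the planned strategy. It is zero if none are dropped, and a gap near 9 points needs five removals, a number the protocol neither gives nor implies.

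For 30-day MACCE (MACE in Section 6.1), bias is possible if imaging or exclusion differs by arm; its direction and size are not established.

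This should be corrected before analysis. Sections 3.2 and 3.3 say that no outcomes have been analysed, so it still can be.

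**What to change.** 1. Reconcile Sections 3.1, 4.2, 4.3 and 8 on when the CT is done and what follows from it, including the two wordings of the aortic criterion. Delete the screen-failure label for randomized patients and the sentence claiming that the integrity of randomization is preserved.
2. Keep every randomized patient, including those already removed on CT, in the intention-to-treat set under the allocated arm. Collect their 30-day outcomes where possible, and report the number and reasons for removal by arm.
3. Report feasibility on all patients randomized to MICS, counting those excluded on CT as not completing the planned strategy. Give the CT-eligible denominator as a labelled sensitivity analysis.
4. For patients still to enrol (100 − 60 = 40 at the August 2025 status in Section 3.2), where a CT is going to be done, complete and read it before the REDCap randomization step. This does not require a CT in patients who would not otherwise have one.

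The cost is revised wording, some extra follow-up of patients already removed, some delay to randomization in elective and urgent cases, and possibly a lower reported feasibility rate. How removed patients are treated clinically is not at issue.

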### 4.3. Eligibility assessment

Clinical and anatomic eligibility for both minimally invasive and conventional CABG is determined by the coronary surgical team. The assessment includes coronary angiographic evaluation (SYNTAX score and target vessel distribution), ventricular function, comorbidities, and overall clinical stability.

Anatomic suitability requires the presence of good distal coronary targets (diameter >1.5 mm) and, whenever predictable from coronary angiography, the avoidance of intramyocardial coronary targets, as well as the potential for achieving complete revascularization based on coronary anatomy.

Other prerequisites include the absence of significant calcification or stenosis in the ascending aorta, its major branches, and femoral arteries (to evaluate the feasibility of peripheral cannulation for cardiopulmonary bypass if required). Preoperative chest CT is reviewed to assess thoracic anatomy, lung expansion, and parenchymal conditions. Patients with sternal deformities precluding either surgical approach are excluded.

## 5. Interventions

MICS CABG vs. conventional CABG via sternotomy.

Both techniques will follow the institutional surgical standards for complete coronary revascularization. The use of on- or off-pump approach will be left to the discretion of the operating surgeon in both study arms.

Graft configuration and overall surgical strategy are similar in both groups, differing only by the access route. Arterial grafts (LIMA, RIMA, or radial) are used according to routine institutional practice, but not systematically in all cases. It depends on patient’s baseline characteristics such as age, diabetes, obesity, grade of coronary stenosis and quality of distal targets. Saphenous vein grafts and radial arteries are typically anastomosed proximally to the ascending aorta, unless intraoperative factors such as graft kinking, limited length, or an unfavorable aortic position necessitate a composite Y- or T-fashion connection to the LIMA.

### 5.1. MICS-CABG group

After anesthetic induction, patients will be intubated using a double-lumen cannula to allow single right lung ventilation. The patient will be positioned at a 30-degree lateral tilt to optimize rib spreading and lateral visualization. The surgical incision will be made in the 4th or 5th left intercostal space, approximately 8 cm in length, at the midclavicular line with medial or lateral extension if needed.

The left internal mammary artery and, if necessary, the right internal mammary artery will be dissected under direct vision using a standard electrocautery device and the Thoratrak® retractor (Medtronic), positioned with the aid of the Rultract Skyhook®. Saphenous vein and radial artery conduits will be harvested via conventional incisions.

The ascending aorta will be accessed through the left anterior mini-thoracotomy by gentle displacement toward the incision. This is achieved using cardiac tape between the aorta and pulmonary trunk or by placing a small gauze pad posteriorly to the aorta. Those maneuvers bring the aorta anteriorly within the operative field, allowing safe clamping and performance of proximal anastomoses under direct vision.

**In off-pump cases**, external suction stabilizers (Octopus Nuvo® and Starfish®, Medtronic) will be introduced through counter-incisions in the subxiphoid region and the 6th or 7th intercostal space and fixed using lateral arms attached to the operating table (Karl Storz®). Proximal anastomoses will be performed either directly on the aorta using an aortic punch (to create the opening for anastomosis) or in a Y-fashion with the LIMA. Intracoronary shunts will be used for distal anastomoses.

**In on-pump cases**, femoral artery and vein cannulation will be performed. A Chitwood aortic clamp will be introduced through the left 2nd intercostal space at the anterior axillary line. Blood cardioplegia will be administered via a long needle. After cross-clamping, tapes will be passed around the aorta, inferior vena cava, and left pulmonary veins to facilitate cardiac rotation and exposure of target vessels [18].

Intraoperative assessment of graft quality will be performed using transit time flow measurement (Medistim®). At the end of the procedure, drains will be placed through the same counter-incisions.

### 5.2. Conventional CABG group

Surgery will be performed through median sternotomy. Graft harvesting will include the left internal mammary artery, right internal mammary artery, and/or saphenous vein or radial artery, using standard techniques.

**In on-pump cases**, cardiopulmonary bypass will be established via central aortic and right atrial cannulation. Myocardial protection will be achieved using blood cardioplegia after aortic cross-clamping. Distal and proximal anastomoses will be performed under direct vision.

**In off-pump cases**, stabilization of the target coronary arteries will be performed using conventional suction stabilizers and positioning techniques. Proximal anastomoses will be performed directly on the aorta, or using composite grafts (Y-grafts), depending on anatomical feasibility.

## 6. Outcomes

### 6.1. Primary

**Feasibility**, defined as the successful completion of the planned minimally invasive coronary revascularization strategy without conversion to sternotomy.**Safety**, assessed by the occurrence of major adverse cardiovascular events (MACE) within 30 days postoperatively.

### 6.2. Secondary

**Complete revascularization rate**, defined anatomically by the treatment of all significant ischemic territories.**Operative metrics**, including surgery duration and intraoperative conversion rates:Off-pump to on-pump conversion (in either surgical access group)Mini-thoracotomy to sternotomy conversion.**Graft quality assessment**, using intraoperative transit time flow measurement (TTFM).**Postoperative recovery parameters**, including:

Duration of mechanical ventilation (hours)

Length of ICU and hospital stay (days)Postoperative bleeding volumeBlood transfusion rate.

**Adverse events**, such as:Postoperative atrial fibrillationWound infection rateStroke (type and severity)Myocardial infarction (type and size, classified as procedure-related or spontaneous)Cause of death (cardiac vs. non-cardiac)**Patient-reported outcomes**, including postoperative pain and quality of life, assessed using the EQ-5D-5L questionnaire.

Detailed descriptions of the prespecified outcomes, definitions, assessment methods, and timing are provided in S1 Table A (Study Variables and Definition).

